### Quality control and trial management

The management structure comprises principle investigators (PI), a Trial Management Group, a Data Monitoring Committee, and a Trial Steering Committee. The Trial Management Group is responsible for the day-to-day delivery and for conducting the trial. It will comprise a project manager and investigators from the GPHCM. The Trial Management Group will meet weekly to discuss trial progress. The project manager will have a face-to-face meeting with the PI every other week. The role of the Data Monitoring Committee is to review safety and efficacy data and to make recommendations to the Trial Steering Committee. It will comprise four fully independent members: one chairman, one oncologist, one senior biostatistician, and one clinical pharmacology expert from the GPHCM. The Data Monitoring Committee will meet once, prior to the start of patient recruitment, and at least once a year for those years in which patients are involved in exercise sessions. The Trial Steering Committee is responsible for approval of any amendments to the main study protocol and, to monitor the trial, steering it towards its overall objectives, to approve and comment on project deliverables, to consider the recommendations of the Data Monitoring Committee, and to resolve any problems brought up by the Trial Management Group. It will comprise one independent chairman, [name], [name], [name], and two other independent members including at least one patient and a public involvement representative. Responsibility for calling and organizing the Trial Steering Committee meetings lies with the PI. The Trial Steering Committee will meet at least annually, more frequently if needed. Representatives of the Data Monitoring Committee are to be invited to all Trial Steering Committee meetings. Before recruitment, the whole research team, including investigators, research assistants, and research nurses will be required to attend a training workshop. This will be done before the trial to ensure their strict adherence to the study protocol and familiarity with the trial administration process. The data collected in this trial will comprise information recorded in case report forms and questionnaires.

Data will be entered using the double-entry method. Data quality will be checked regularly by research assistants and overseen by monitors. Data monitoring will be conducted regularly with standard operation procedures by a team from the GPHCM Key Unit of Methodology in Clinical Research. Inspections will be performed regularly by the GPHCM Department of Science Research. All modifications are to be marked on the case report forms. Data managers will then recheck the data before logging it. The database will be locked after all data have been cleaned. If participants withdraw from the trial during the study period the reasons must be documented, and the dropout rate is to be statistically analyzed.

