#### Control group

Patients in the control group will receive only conventional therapy according to national guidelines.

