#### Intervention group

Patients in the treatment group will receive a 5-day Shenmai injection regimen plus conventional therapy. According to national guidelines, conventional therapy includes the routine use of antiemetic and gastro-protective agents. SMI will be manufactured by Huarun Ya’an Sanjiu Pharmaceutical Co., Ltd., based on good manufacturing practice (GMP) standards. Each milliliter of the injection is equivalent to 0.1 g of red ginseng (*Radix ginseng Rubra*) and 0.1 g dwarf lilyturf tuber (*Radix ophiopogonis*) of crude drug. It will be administered at a dose of 100 ml by intravenous infusion once daily for 5 days as a period. Treatment will be administered by Chinese medicine physicians with 5 years of formal university training in Chinese medicine, a license to administer treatment, and at least 1 year of clinical experience.

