### Safety

An independent Data and Safety Monitoring Committee will evaluate the progress of the study and assess the safety data, as requested during the study. Adverse events (AEs) will be defined as any undesirable experience participants endure during the trial period, regardless of whether or not it is associated with the intervention. Participants will be instructed to report AEs to the research team, and a research nurse will monitor participants for potential occurrences of AEs. All details of AEs, such as time of occurrence, severity, management, and causality to the intervention, will be recorded on case report forms. All AEs will be followed up from the date they are brought to the investigator’s attention until resolution. Severe AEs must be reported to both the GPHCM Data and Safety Monitoring Committee and the GPHCM Ethics Committee within 24 h. Severe AEs will be defined according to the International Conference on Harmonization guidelines [41]; any adverse event will be regarded as serious if it results in death, is life-threatening, requires hospitalization or prolongation of existing hospitalization, or results in persistent or significant disability or incapacity.

To assess safety, we will perform the following tests on participants at the screening phase (baseline) and on day 5 (the end of the intervention): routine blood, routine feces, routine urine, liver, and kidney function, and electrocardiography. Safety will be assessed according to the National Cancer Institute Common Terminology Criteria for Adverse Events, version 4.0.

In particular, we will pay attention to adverse drug reactions (ADRs) associated with SMI. Because of its effectiveness, the scope of diseases treated with SMI has gradually broadened, and reports of associated adverse reactions have increased correspondingly. The number of published literatures has ranked SMI ninth for ADRs in 33 varieties of Traditional Chinese Medicine injections in the 2004 edition of the National Essential Drugs List (2004 edition) in China [42].

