### Trial status

Recruitment started in December 2017, and it is expected to finish in April 2019.

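### The Data Monitoring Committee's meeting rule depends on exercise sessions that this trial does not have, so as written it schedules no committee meeting during recruitment

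*Protocol article*

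**What the plan says.** The section on quality control and trial management sets out the committee's task and its timetable. On the task: "The role of the Data Monitoring Committee is to review safety and efficacy data and to make recommendations to the Trial Steering Committee". On the timetable: "The Data Monitoring Committee will meet once, prior to the start of patient recruitment", and after that "at least once a year for those years in which patients are involved in exercise sessions".

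The intervention sections describe the two arms. For the intervention group: "Patients in the treatment group will receive a 5-day Shenmai injection regimen plus conventional therapy". For the control group: "Patients in the control group will receive only conventional therapy according to national guidelines". The only content given for the shared background treatment is that "conventional therapy includes the routine use of antiemetic and gastro-protective agents".

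The Safety section describes the monitoring body under a different name and gives no frequency: "An independent Data and Safety Monitoring Committee will evaluate the progress of the study and assess the safety data, as requested during the study". It also requires severe adverse events to reach that body and the Ethics Committee within 24 h.

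On timing, the Trial status section says: "Recruitment started in December 2017, and it is expected to finish in April 2019".

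**The concern.** The only rule that sets committee meetings after recruitment opens is tied to an activity foreign to this trial. It reads like text written for an exercise programme. This is not a detail that a condensed article may leave to a charter: the article states a schedule, and the schedule does not fit the design.

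At stake is a planned look at accumulating safety data while patients are still being treated. Patients and treating staff know the allocation, and the patients have stage IIIB to IV disease and are on chemotherapy. The protocol itself lists allergic shock among the main reactions reported with the product and promises particular attention to such reactions. Case-by-case reporting shows single events. Only a review across patients and arms shows a pattern. If the clause is followed as written, the one meeting it requires takes place before any patient data exist. If staff silently reinterpret it, different readers may apply it differently.

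**Working it through.** No power or error-rate calculation is involved. The check is a reading of the text followed by date arithmetic.

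**Step 1. Is there an exercise component?**

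| Place in the protocol article | What is described | Exercise? |
|---|---|---|
| Design | 5-day infusion regimen plus conventional therapy, against conventional therapy | No |
| Control group | Conventional therapy only | No |
| Intervention group | Daily infusion for 5 days; conventional therapy with antiemetic and gastro-protective agents | No |
| Outcome measures and assessments, primary and secondary outcomes | Questionnaires, physiological tests and blood samples at baseline and day 5 | No |

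Figures 1 and 2 are not available here, but the text that refers to them describes no such component.

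**Step 2. The recruitment window.** December 2017 to April 2019:

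- elapsed months: (2019 − 2017) × 12 + (4 − 12) = 16
- calendar months counted inclusively: 16 + 1 = 17
- calendar years touched: 2019 − 2017 + 1 = 3
- 12-month periods, rounded up: 17 / 12 = 1.4, so 2

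**Step 3. Meetings required after the pre-recruitment one.** The minimum is 1 × (number of years in which the condition holds).

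- As written, years with exercise sessions = 0, so 1 × 0 = **0 meetings**.
- With the condition changed to years with patients on study, 1 × 2 = **2 meetings** by 12-month periods, or 1 × 3 = **3 meetings** by calendar years. On the calendar count, 2017 contributes only December, and 2019 only January to April.

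**Step 4. Does another passage supply the schedule?**

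- The Safety section's review on request names no requester and no interval.
- The 24 h rule for severe adverse events is expedited reporting of individual cases.
- The Trial Steering Committee meets at least annually and invites representatives of the monitoring committee. Its task is to consider that committee's recommendations, and no in-trial meeting is scheduled to produce them.

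Each is a real safeguard, but none fixes a date or interval for a committee review.

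**Step 5. Name and independence.** The Safety section speaks of a Data and Safety Monitoring Committee and, in the reporting rule, attaches the GPHCM's name to it. The quality control section speaks of a Data Monitoring Committee with four members, all described as independent, and then places at least the clinical pharmacology expert at the GPHCM. The GPHCM's branch hospitals recruit the patients, and its investigators sit on the Trial Management Group. The sections do not say whether the two names mean one body, or what independence means for a member from the GPHCM.

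**The case against.** The strongest reply is that this is a wording slip with an obvious intended meaning, in a trial that has other protection. Much of that stands. Severe events reach the committee within 24 h, a research nurse monitors for adverse events, and the Steering Committee meets at least annually. The protocol also says that the product has a lower rate of adverse reactions and that most occurred in the first 30 minutes of the first administration, a period for which it asks for close observation. For acute reactions, bedside observation and rapid reporting are the main safeguards. The rule also sets a minimum, so the committee is free to meet more often.

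Three stronger readings are tempting, and the document does not support them:

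- **That the trial has no safety oversight or no safety review.** The routes above contradict this. What is missing is a scheduled committee review.
- **That even an annual reading brings the committee in too late.** A first meeting at month 12 of 16 would come after 12 / 16 × 94 = 70.5, or about 70, of the 94 patients, if accrual were uniform. But the text sets a minimum and names no month, so the first meeting could fall much earlier. The figure is a late case. Nor does the document show that annual review is wrong for a trial of 94 patients.
- **That the chair and the biostatistician are GPHCM staff and must be replaced.** In the membership list, the reference to the GPHCM may belong only to the pharmacology expert.

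What the reply does not remove is that the stated condition is never met and no other passage replaces it.

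**Conclusion.** The point holds in a limited form. As worded, the rule requires 0 Data Monitoring Committee meetings during recruitment, against at least 2 or 3 if it were tied to years with patients on study. The count rests on two assumptions: that the clause is read literally, and that the figures not available here contain no exercise component, as the surrounding text indicates. The difference in committee name and the unclear claim of independence are smaller points of consistency.

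This is an error of wording with a consequence for planned safety review. It does not touch the primary outcome, the sample size or the final test.

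**What to change.** Replace the reference to exercise sessions with a trigger that exists in this trial. One form is a meeting at a stated interval for as long as patients are being recruited and treated, with at least one early enough in the window of roughly 16 months for its recommendations to be acted on. The choice of interval belongs to the sponsor and the committee.

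Use one committee name in the Safety section and in the section on quality control and trial management, or state that there are two bodies and what each does. Say which members belong to the GPHCM, and word the claim of independence to match. The committee's stated role of reviewing both safety and efficacy data can stay as it is; correcting the trigger neither requires narrowing that role nor adds a stopping rule.

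The cost is one clause of wording, a consistency edit, and a small number of meetings of a committee that already exists. Sample size and the final test are unaffected.

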## Discussion

CFR is a common and unavoidable side effect of current forms of cancer treatment. It interferes with daily activities of cancer patients and affects various aspects of life, including physiological, social, and psychological well-being [45]. The National Comprehensive Cancer Network provides an evidence-based guideline that includes pharmacological and nonpharmacological interventions [46]. However, it does not include TCM, which relieves the symptoms of CRF effectively. The use of Chinese herbal injections for treatment of CRF should adopt an evidence-based approach.

This study has some limitations. First, due to the nature of the intervention, blinding is impossible. We will make every effort to ensure that outcome assessors, laboratory technicians, data managers, and statisticians are unaware of the treatment allocations. Another limitation is the 5-day treatment period which does not have a follow-up. While many studies use 1- or 2-week treatment periods in the clinical trial setting [47, 48], it would be appropriate in future studies to administer treatment for longer periods with long-term follow-up research since fatigue is a chronic symptom and, in most cases, affects patients for far longer than several weeks. This could make the results more convincing.

Considering that SMI originated and developed mainly from the traditional medicinal system in China, which considered the constitution or specific characteristics of health status in prescribing medication, the concurrent use of outcome measurements reflecting the perspective of traditional medicine will be of interest in future studies. In traditional medicine in China, SMI is not prescribed for everyone but for those with *qi*-deficiency syndrome, which is defined as a hypersensitive, easily fatigable state [49]. Although fatigue is one of the typical symptoms of this *qi*-deficiency syndrome, other factors that constitute the syndrome may also be considered in studying SMI.

Despite its limitations, we believe that this study has the potential to contribute to the development of an effective intervention to help relieve CRF. It will also establish feasibility and provide preliminary evidence on the efficacy and safety of SMI in advanced NSCLC patients with CRF. Based on the results of the study, future studies should employ more subjects, establish an appropriate control group, and include long-term administration and follow-up.

### Trial status

Recruitment started in December 2017, and it is expected to finish in April 2019.

## Abbreviations

ADR: Adverse drug reaction
AE: Adverse event
CRF: Cancer-related fatigue
ECOG: Eastern Cooperative Oncology Group
ESAS: Edmonton Symptom Assessment Score
FACIT-F: Functional Assessment for Chronic Illness Therapy-Fatigue
FACT-L: Functional Assessment of Cancer Therapy-lung
GMP: Good manufacturing practice
HADS: Hospital Anxiety and Depression Scale
NSCLC: Non-small cell lung cancer
PSQI: Pittsburg Sleep Quality Index
QOL: Quality of life
RCT: Randomized controlled trial
SMI: Shenmai injection
TCM: Traditional Chinese medicine
TNF: Tumor necrosis factor
